### Statistical methods

#### Sample size

The PICnIC pilot study is set up to test the feasibility of the protocol to recruit eligible patients. Therefore, there is no primary outcome to be compared between the two groups and, hence, a usual power calculation to determine sample size is not appropriate. Instead, the sample size has been determined to be adequate to estimate critical parameters to be tested to a necessary degree of precision. Based on available data from PICANet, it is anticipated participating sites will see approximately 4.5 eligible children per week, therefore, the anticipated recruitment rate is three children per PICU per week providing a total of approximately 324 children in 18 weeks, of which 90 would receive the intervention. The sample size of children receiving usual care would be sufficient to estimate a binary outcome present in 20% of the population with a precision of ±5%.

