**Methods and analysis:**

Paediatric Intensive Care and Infection Control is a parallel group pilot cRCT, with integrated mixed-methods study, comparing incorporation of SDD into infection control procedures to standard care. After a 1-week pretrial ecology surveillance period, recruitment to the cRCT will run for a period of 18 weeks, comprising: (1) baseline control period (2) pre, mid and post-trial ecology surveillance periods and (3) intervention period. Six PICUs (in England, UK) will begin with usual care in period 1, then will be randomised 1:1 by the trial statistician using computer-based randomisation, to either continue to deliver usual care or commence delivery of the intervention (SDD) in period 2. Outcomes measures include parent and healthcare professionals’ views on trial feasibility, adherence to the SDD intervention, estimation of recruitment rate and understanding of potential patient-centred primary and secondary outcome measures for the definitive trial. The planned recruitment for the cRCT is 324 participants.

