### Study setting

Six PICUs based in England, UK with a diverse geographical/demographic population representative of national (UK) PICU activity and size.

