### Design

External pilot, parallel group cRCT with integrated mixed-methods study. After a 1-week pretrial ecology surveillance period, recruitment to the cRCT will run for a period of 18 weeks, comprising: (1) baseline control period (‘period 1’—weeks 2–9); (2) mid-trial ecology surveillance period (week 10) and (3) intervention period (‘Period 2’—weeks 11–19). On completion of period 2, an additional 1-week post-trial ecology surveillance period will be carried out (figure 1). Sites will be randomised 1:1 by the trial statistician using computer-based randomisation, to either continue to deliver usual care or commence delivery of the intervention (SDD) in period 2 (figure 2).

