### Trial intervention

During the Ecology Surveillance periods, period 1 and for sites randomised to usual care in period 2, there is no intervention. Patients will receive all standard infection control measures (per the site’s specific policies) but will receive no study specific intervention.

For sites randomised to the intervention in period 2, it will form part of the standard infection control strategy in the participating PICU. In addition to usual care, an SDD-enhanced infection control regimen will be delivered to all eligible patients using a Good Manufacturing Practice (GMP)-certified commercial SDD preparation under licence from The George Institute, Australia (Verita Pharma Pty, Australia). (Within online supplemental file 1, online supplemental table 1) for SDD administration details, (online supplemental tables 2 and 3) for composition and characteristics of SDD, (online supplemental tables 4 and 5) for SDD formulation, online supplemental appendix 1 for GMP licence, online supplemental appendices 2–8 for SDD stability data and online supplemental appendix 9 for PICnIC labels). Dosing of the SDD suspension will be calculated according to age (table 1):

10.1136/bmjopen-2022-061838.supp1Supplementary data

**Table 1 T1:** SDD suspension dosing

	0–4 years	5–12 years	≥13 years
Polymyxin E (Colistin)	25 mg	50 mg	100 mg
Tobramycin	20 mg	40 mg	80 mg
Nystatin	0.5×106 IU	1×106 IU	2×106 IU
	2.**5** mL	**5** mL	10 mL

SDD, Selective Decontamination of the Digestive.

A 6 hourly topical, application of a pea-sized (0.5 g) SDD paste containing 2% polymyxin E (colistin), 2% tobramycin and 2% nystatin to the buccal mucosa and oropharynx.A 6 hourly administration of SDD suspension administered via the most proximal feeding tube into the stomach containing polymyxin E (colistin), tobramycin and nystatin.

SSD preparations will be distributed by the manufacturer in temperature-controlled (2°C–8°C), patient specific kits to the participating hospital pharmacies. Each kit contains a 5-day supply of SDD treatment which includes a bottle of SDD suspension powder for reconstitution and 20×1 mL syringes containing Oral Paste. When a kit is allocated to a patient and the SDD powder is reconstituted into suspension, the kit can be stored at room temperature (≤27°C) for up to 5 days. SDD treatment should be started within 6 hours of the patient being identified as eligible and continue for a maximum of 30 days (treatment period).

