### Consent procedures

Children who are eligible for PICnIC will often become so during a period of life-threatening illness. This is a stressful time for parents/guardians during which time there are ethical concerns both about the burden placed of trying to understand the trial and their ability to provide informed consent.^17^

Posters displayed throughout the PICU will explain ecology sampling procedures and invite parents/guardians to have further discussions with research staff. The SDD intervention will be delivered, in additional to standard infection control policies, to all eligible patients in sites randomised to the SDD intervention during period 2. Research staff will not seek individual consent for this. This approach is in line with guidance from the Ottawa Statement on the ethical design and conduct of cRCT.^18 19^ (See online supplemental file 2) for poster and consent forms).

10.1136/bmjopen-2022-061838.supp2Supplementary data

Consent will be required for:

Any additional study-specific samples to be taken, stored and analysed prior to being taken solely for the study and not as part of routine care.Identifiable data collected and processed for participation in the mixed methods aspects of the study (questionnaire and interview).Monitoring of medical records.

Consent will not be required for:

Samples taken as part of routine care (eg, admission samples).Anonymised data collection and processing from routine sources.Delivery of SDD. For PICUs randomised to the intervention during period 2, all children meeting the eligibility criteria will receive SDD as the standard practice.

Children may be withdrawn from trial-specific data collection by the request of parents who decline participation in the research. All data collected up to the point of withdrawal will be retained and included in the study analysis.

If the patient has died, the parents/guardians will be approached for consent for the monitoring of medical records and identifiable data collected, and for the interview aspect of the study once established whether it is appropriate to approach for consent.

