### Outcome measures

As this is a pilot study, outcome measures for the study will be focused on assessing the feasibility of a larger scale definitive study.

The ability to randomise PICUs to either control or intervention will be assessed by the successful random assignment of three PICUs to the intervention without delay to subsequent phases of the trial.

The willingness and ability of healthcare professionals to screen and recruit eligible children will be assessed by the proportion of eligible children recorded on study screening logs successfully recruited to the pilot cRCT and the reported reasons for non-recruitment.

The potential recruitment rate for a future definitive cRCT trial of SDD-enhanced infection control in eligible children will be estimated by combining the proportion of eligible children recruited to the pilot cRCT with the size of the potentially eligible population (estimated from nesting the screening log data from participating PICUs within the national UK PICU data from PICANet).

Adherence to the SDD protocol will be assessed by the proportion of eligible children allocated to the intervention receiving (1) both elements and (2) each individual element of the SDD intervention, the number of days on which these elements were received relative to days eligible for the SDD intervention and the reported reasons for nonadherence.

Procedures for assessing and collecting selected clinical and ecological outcomes and for AE reporting will be assessed by the proportion of children with complete data for these outcomes including, for ecological outcomes, the proportion consenting to additional study specific sample collection.

Generalisability of the study results to all UK PICUs will be assessed by comparing baseline characteristics and outcomes for children recruited to the pilot cRCT with data from all potentially eligible children (receiving invasive mechanical ventilation for at least three calendar days) within participating PICUs and within all UK PICUs (from PICANet).

With the aim of understanding potential patient-centred primary and secondary outcome measures for the definitive cRCT, the following potential outcome measures will be reported:

HCAI (confirmed/presumed) and microbiology results (if positive sample).Hospital mortality.PICU mortality.Mortality within 30 days postenrolment.Length of hospital stay.Length of stay in PICU.Duration of mechanical ventilation.Organ support received.

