#### Analysis

An overview of the planned analyses for the PICnIC pilot study is provided below. The full statistical analysis plan will be lodged on the trial website ahead of database lock.

A Consolidated Standards of Reporting Trials flow diagram will be used to summarise the number and percentage of children screened, recruited and followed up. This will include the proportion of eligible children successfully recruited and the reported reasons for non-recruitment.

Recruitment to the pilot cRCT will be presented as a rate per site per week over the two recruitment periods, overall, by treatment group and by site. Potential reasons for variation in recruitment rates will be explored. The potential recruitment rate for a future definitive cRCT will be estimated by combining the proportion of eligible children recruited to the pilot cRCT with the size of the potentially eligible population (estimated from PICANet).

Baseline demographic and clinical data will be summarised overall and for each of the two treatment groups in each of the two time periods but not subjected to statistical testing.

The proportion of eligible children allocated to the intervention that received both elements and each individual element of the SDD intervention will be reported as well as the number of days on which these elements were received relative to days eligible for the SDD intervention. The reported reasons for nonadherence will be detailed.

Data completeness of clinical and ecological outcomes and for AE reporting will be summarised.

Patient characteristics for children recruited to the pilot cRCT will be compared with those for potentially eligible children within participating PICUs and within all UK PICUs.

Potential patient-centred clinical outcome measures for the definitive trial will be estimated and reported (proportion or mean and SD, and intracluster correlation). As a pilot cRCT, there will be no statistical testing for any of the summary measures. Comparisons between groups will be used to estimate the potential magnitude of the treatment effect; p values will not be calculated or quoted.^20^ To account for cluster randomisation, we will use multilevel logistic or generalised linear regressions in the above analyses.

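### The planned 90 children receiving SDD should be 81 on the protocol's own sites, rate and calendar, and the recruitment status of week 10 needs reconciling

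*Protocol article*

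**What the plan says.** All places are in the protocol article.

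- **Sample size:** at three children per unit per week, the plan expects "a total of approximately 324 children in 18 weeks, of which 90 would receive the intervention". The abstract repeats the total: "The planned recruitment for the cRCT is 324 participants".
- **Study setting and Outcome measures:** there are "Six PICUs based in England, UK", and the ability to randomise is judged by "successful random assignment of three PICUs to the intervention".
- **Design:** recruitment lasts 18 weeks, made up of period 1 (weeks 2–9), then the "mid-trial ecology surveillance period (week 10) and (3) intervention period", which is period 2 (weeks 11–19).
- **Trial intervention:** "During the Ecology Surveillance periods, period 1 and for sites randomised to usual care in period 2, there is no intervention". SDD is therefore given only in period 2, and only in the three units allocated to it.
- **Eligibility headings:** one set of criteria covers the ecology surveillance periods and admits every patient on the unit. A separate set, for ventilated children, is headed for periods 1 and 2.
- **Analysis:** "Recruitment to the pilot cRCT will be presented as a rate per site per week over the two recruitment periods". Baseline data are summarised by treatment group in each of two time periods.

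**The concern.** The sample size sentence gives a total and a subset. Both should come from the same rate, number of units and calendar. The total does, but the subset is larger than nine weeks of SDD delivery in three units can give at the stated rate.

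There is a second, softer problem. Week 10 is a recruitment week in the Design section, but the trial eligibility criteria and the reporting of recruitment are set out for two periods that leave it out. The article therefore does not say under which criteria a child is recruited in week 10, or where that child is counted.

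What is at stake is the planned size of the only group that informs adherence to and tolerance of SDD, and the number of weeks by which a recruitment rate per site per week will be divided. Both are headline design figures in a feasibility study, although no hypothesis test depends on them.

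**Working it through.** **Inputs**

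- Units: 6 (Study setting); units giving SDD: 3 (Outcome measures).
- Rate: 3 recruited children per unit per week (Sample size).
- Period 1: weeks 2–9 = 8 weeks. Mid-trial ecology: week 10 = 1 week. Period 2: weeks 11–19 = 9 weeks (Design).
- SDD weeks: period 2 only = 9 (Trial intervention).

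**Step 1: the plan's total.** Weeks: 8 + 1 + 9 = 18. Total: 6 × 3 × 18 = 324. This reproduces the stated figure exactly.

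**Step 2: the SDD count.** SDD units × rate × SDD weeks:

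| SDD weeks | Children under SDD |
|---|---|
| 8 | 3 × 3 × 8 = 72 |
| 9 (as designed) | 3 × 3 × 9 = 81 |
| 10 | 3 × 3 × 10 = 90 |

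The stated 90 needs 90 / (3 × 3) = 10 weeks, or a rate of 90 / (3 × 9) = 3.33 per unit per week over 9 weeks. The article states neither. The excess is 90 − 81 = 9 children, which is 9 / 81 = 11%.

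**Step 3: the usual-care count and week 10.**

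- As implied by the article: 324 − 90 = 234.
- Week 10 recruits, and its recruits count as usual care: 324 − 81 = 243.
- Week 10 does not recruit: 8 + 9 = 17 weeks, total 6 × 3 × 17 = 306, usual care 306 − 81 = 225.

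**Step 4: effect on precision.** The 95% half-width for a proportion of 20% is 1.96 × √(0.2 × 0.8 / n), ignoring clustering.

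| Group | n | Half-width (percentage points) |
|---|---|---|
| Usual care, as implied | 234 | ±5.13 |
| Usual care, week 10 included | 243 | ±5.03 |
| Usual care, week 10 excluded | 225 | ±5.23 |
| SDD, as stated | 90 | ±8.3 |
| SDD, recomputed | 81 | ±8.7 |

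The article's only precision statement, ±5% for usual care, holds on rounding in every case. It states no precision target for the SDD group.

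**The case against.** **Could 90 be a rounded figure?** The word of approximation is attached to 324, which is in fact exact. Rounding does not explain a gap of 9 children.

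**Could children enrolled before week 11 and still ventilated in period 2 add to the count?** Possibly, but the article neither describes them as SDD recipients nor uses them in the calculation. A reader may also suppose that week 10 was counted as an SDD week. That fits the arithmetic but is an inference: the article shows only that 90 equals ten weeks at the stated rate.

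**Is 324 wrong as well?** A reader might infer this from the two-period wording. The documents do not support it, because the Design section expressly places week 10 inside the 18 weeks of recruitment. The figure 306 is what follows if week 10 is excluded; it is not a correction that the documents compel. It can also be said that usual care is the natural class for week-10 recruits, since no intervention is given then, and that assigning them to an analysis period is detail for the analysis plan. That largely stands, and it leaves only a need to make the sections agree.

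**Should the figure be about 122?** SDD is delivered without individual consent: "all children meeting the eligibility criteria will receive SDD as the standard practice". At 4.5 eligible children per unit per week, 3 × 4.5 × 9 = 121.5 children would be exposed. But the 90 is a subset of 324 recruited children, so 122 is a different quantity and is no check on it.

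**Would feasibility be judged against a wrong target, or the target be out of reach?** The article does not support either reading. Its measures are the proportion of eligible children recruited, with reasons for non-recruitment, and a rate per site per week. Nor is 324 unreachable in 17 weeks: it would need 324 / (6 × 17) = 3.18 per unit per week, against 4.5 eligible.

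**Conclusion.** The SDD figure is wrong as written, and the error is minor. On the article's own inputs, 81 recruited children would receive SDD, not 90. This rests on three SDD units, the stated rate of three per unit per week applying equally in all units and weeks, and no SDD outside weeks 11–19, as the Trial intervention section says.

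The total of 324 stands on the Design section's definition of the recruitment weeks. That definition does not match the two-period wording of the eligibility heading and the Analysis section, and these places must be reconciled.

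The practical effect is modest. There is no power calculation, the usual-care precision claim survives, and the SDD half-width at 20% widens by about 0.4 points. If 324 is kept and 90 becomes 81, the usual-care group grows from 234 to 243 and its precision improves slightly.

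**What to change.** In the Sample size section, replace 90 with 81 and show the product (3 units × 3 per week × 9 weeks). Then settle week 10 in one of two ways:

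1. **Week 10 recruits to the trial.** Keep 18 weeks and 324. State that week-10 recruits enter under the criteria for periods 1 and 2 and count as usual care (243 usual care, 81 SDD). Amend the eligibility heading and the Analysis wording to match.
2. **Week 10 does not recruit.** Restate the recruitment duration as 17 weeks and the total as 306 (225 usual care, 81 SDD) in the abstract, the Design section and the Sample size section.

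The cost is wording only. The usual-care precision statement of ±5% can stay under either choice (±5.0 or ±5.2 points, ignoring clustering). No change to conduct or to the planned analyses is needed, beyond stating how week-10 recruits are classified.

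### The ±5% precision quoted for usual care treats children as independent; allowing for six PICUs it is about ±6 to ±9 points at assumed ICCs of 0.01 to 0.05

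*Protocol article*

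**What the plan says.** The Sample size section explains that a conventional power calculation does not apply and that instead "the sample size has been determined to be adequate to estimate critical parameters to be tested to a necessary degree of precision". It expects "approximately 324 children in 18 weeks, of which 90 would receive the intervention". The one figure offered in support is that the usual-care group is "sufficient to estimate a binary outcome present in 20% of the population with a precision of ±5" per cent. The section mentions neither an ICC nor a design effect.

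The rest of the article describes a clustered design. Study setting gives "Six PICUs based in England, UK with a diverse geographical/demographic population", and Outcome measures refers to the "successful random assignment of three PICUs to the intervention". Under Analysis, the candidate outcomes are to be reported with their intracluster correlation, and "To account for cluster randomisation, we will use multilevel logistic or generalised linear regressions in the above analyses".

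**The concern.** The sample-size statement and the analysis make different assumptions about the same children. The analysis expects outcomes within a PICU to be correlated. The precision figure matches a simple random sample. If outcomes differ between PICUs, 234 children in six units carry less information than 234 independent children.

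The figure matters because it is the only quantitative support for the sample size, and because usual-care event rates are among the pilot's inputs to a definitive trial. A reader who takes ±5 points at face value would trust those rates too much.

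**Working it through.** **Inputs from the protocol article**
- Total: 6 PICUs × 3 children per week × 18 weeks = 324 (Sample size).
- Intervention: 90 children, so usual care = 324 − 90 = 234 (Sample size).
- Outcome proportion p = 0.20; stated half-width 5 points (Sample size).
- Three PICUs are assigned to SDD (Outcome measures). Period 1, with all sites on usual care, covers weeks 2–9, which is 8 weeks (Design).

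**Assumptions, because the document gives no value**
- Confidence level 95%, z = 1.96.
- ICC between 0.01 and 0.05, with 0.10 shown as an extreme.

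**Step 1: reproduce the stated figure.**
1.96 × √(0.2 × 0.8/234) = 0.0513, or ±5.1 points, which rounds to ±5%. A half-width of exactly 5.0 points needs 1.96² × 0.16/0.05² = 245.9, so 246 children. There is no slack to absorb a design effect.

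**Step 2: usual-care cluster sizes.**
- Three sites on usual care throughout: 18 × 3 = 54 each.
- Three sites that move to SDD: 8 × 3 = 24 each.
- Check: 3 × 54 + 3 × 24 = 234.

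**Step 3: design effect for unequal clusters.**
Σm²/Σm = (3 × 54² + 3 × 24²)/234 = 10,476/234 = 44.8, so DE = 1 + 43.8 × ICC, or about 1 + 44 × ICC.

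**Step 4: half-width = 1.96 × √(0.16 × DE/234).**

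| Assumed ICC | DE | Effective n | Half-width, z = 1.96 | Half-width, t on 5 df |
|---|---|---|---|---|
| 0 | 1.00 | 234 | ±5.1 | ±6.7 |
| 0.01 | 1.44 | 163 | ±6.1 | ±8.1 |
| 0.02 | 1.88 | 125 | ±7.0 | ±9.2 |
| 0.05 | 3.19 | 73 | ±9.2 | ±12.0 |
| 0.10 | 5.38 | 44 | ±11.9 | ±15.6 |

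**Step 5: how small must the ICC be?**
The half-width reaches 5.5 points, and so stops rounding to 5, at an ICC of [(0.055/1.96)² × 234/0.16 − 1]/43.8 ≈ 0.0035.

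**Step 6: sensitivity (ICC 0.01, 0.02, 0.05; z = 1.96).**
- Equal clusters of 39: ±6.0, ±6.8, ±8.7.
- Inverse-variance weighting of sites: ±6.1, ±6.9, ±8.9.
- Nine weeks of SDD recruitment (weeks 11–19) in place of the printed 90 gives 3 × 3 × 9 = 81 SDD children and 243 in usual care (54 and 27 per site): ±6.0, ±6.9, ±9.0.

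None of these choices changes the conclusion.

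**The case against.** Several points on the other side have weight.

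- **The arithmetic is right.** For independent children the figure reproduces. The fault is an unstated assumption that does not fit the design. This stands.
- **The size of the loss is unknown.** It depends on an ICC that the document does not give and that the pilot sets out to estimate. This stands too, so only a range can be quoted.
- **The confidence level is not stated.** At 90% the unclustered half-width is 1.645 × √(0.16/234) = 4.3 points, and an ICC of 0.01 gives 4.3 × √1.44 = 5.2, which would still round to ±5. But the section mentions neither a 90% level nor any clustering allowance, and 95% with no design effect is the plain reading.
- **Lower event rates are estimated more tightly.** The Introduction cites an HCAI prevalence of 7%–14%. At ICC 0.01 the half-widths would be about ±3.9 and ±5.3 points, and at 0.02 about ±4.5 and ±6.1. Roughly ±5 points survives for such rates at low ICCs, but the sentence is about a 20% outcome.
- **The figure could describe these six PICUs alone, as fixed units.** That does not fit the plan to assess generalisability to all UK PICUs, to inform a definitive trial and to use multilevel models.

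A reader might also infer that precision for SDD adherence is misstated. The article claims no adherence precision, so nothing there is wrong as written, and an article may leave that detail to the full protocol or SAP. Nor can one say that published confidence intervals will contradict the plan: the Analysis section promises proportions, means with SDs and ICCs, but not intervals for the usual-care proportions.

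**Conclusion.** The point holds as an unadjusted precision statement in a six-cluster design. Taken as a 95% half-width, ±5% is delivered only if the ICC is below about 0.0035. Under assumed ICCs of 0.01 to 0.05, precision for a 20% outcome in 234 usual-care children is about ±6 to ±9 points with z = 1.96, and about ±8 to ±12 with a t multiplier on 5 degrees of freedom.

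The importance is moderate. No primary outcome is compared and no p values are to be calculated, so no power or type I error claim is affected. It would be wrong to conclude that the pilot is too small or that its analysis ignores clustering. The target of 324 follows from sites, weeks and expected recruitment, and the planned models do account for PICU. What needs correcting is how much certainty the sample-size sentence promises.

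**What to change.** Replace the last sentence of the Sample size section with a cluster-adjusted one, for example: *With about 234 usual-care children in six PICUs, a 20% outcome is estimated to within about ±6 to ±9 percentage points (95% level) for an assumed ICC of 0.01 to 0.05.* Alternatively, keep ±5% and say that it assumes no clustering within PICUs. In either case, state the confidence level.

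The cost is one sentence and a less favourable figure. Recruitment, design and analysis stay as they are.
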